### **15.2 PUBLICATION**

The clinical study report will be submitted to the local HRECs, funding bodies (NHMRC, Norman Beischer Foundation and SOMANZ) and relevant regulatory authorities within one year of the study's completion. A copy will also be forwarded to senior representatives of the Sponsor and the Investigational Sites.

The study report will be used by approved members of the research team to present the results of the trial at scientific meetings. The PIs will have the right to submit/grant permission for the submission of the results of the study for written and/or oral publication.

A summary of the study results will be made available to the other members of the research team, who may, at their discretion, disseminate the findings within their clinics. A lay summary of the results will be made public on the Sponsor's and Investigational Sites' websites, in accordance with ICH-GCP recommendations. A lay summary may also be sent directly to the individual participants of the study, at the discretion of their respective hospital's Site Leader.

### **15.3 PEER REVIEW**

This trial, its ethical acceptability and scientific merit was extensively reviewed by the members of Mercy Health HREC prior to the authorship of the study protocol or the commencement of study recruitment. The HREC panel includes academic, medical and midwifery specialists; ethicists; and lay-people.

**APPENDIX 1: Manufacturer's (Pfizer Australia) Product Information – Salazopyrin (sulfasalazine)**

Retrieved from: <http://secure.healthlinks.net.au/content/pf/retriever.cfm?product=pfpsalaa10913>

## PRODUCT INFORMATION

### SALAZOPYRIN® and SALAZOPYRIN® EN-TABS (sulfasalazine)

#### NAME OF THE MEDICINE

SALAZOPYRIN (sulfasalazine) 500 mg tablets.

SALAZOPYRIN EN-TABS (sulfasalazine) 500mg enteric coated tablets.

The structural formula of sulfasalazine is shown below:

[figure not shown]

Chemical Name: 2-Hydroxy-5-[2-[4-(pyridin-2-ylsulphamoyl)phenyl]diazenyl]benzoic acid  
Molecular Formula: C13H14N4O5S  
Molecular Weight: 398.4  
CAS Registry Number: 599-79-1.

#### DESCRIPTION

Sulfasalazine is a bright yellow or brownish-yellow, fine powder. It is practically insoluble in water, very slightly soluble in ethanol (96 percent), practically insoluble in methylene chloride. It dissolves in dilute solutions of alkali hydroxides.

SALAZOPYRIN tablets contain 500 mg of sulfasalazine and the following inactive ingredients: starch-maize, silica-colloidal anhydrous, magnesium stearate, and povidone.

SALAZOPYRIN EN-TABS enteric coated tablets contain 500 mg of sulfasalazine and the following inactive ingredients: starch-maize, silica-colloidal anhydrous, magnesium stearate, cellacephate, propylene glycol, beeswax-white, carnauba wax, macrogol 20000, glyceryl monostearate, and talc-purified.

## PHARMACOLOGY

### Pharmacodynamics

Sulfasalazine has, among others, an immunosuppressive effect and has shown affinity to connective tissue. It has also been shown to have a wide range of effects in other biological systems. It is, however, difficult to judge the clinical relevance of its various pharmacological actions since the aetiology of rheumatoid arthritis is largely unknown. Moreover, the mode of action of sulfasalazine in the treatment of ulcerative colitis is also not known. A metabolite of the drug may have an inhibitory effect on an antigen-antibody process occurring in the intestinal wall and the salicylate component may act as an anti-inflammatory agent. The drug does not appear to have any long term antibacterial effect on the stool flora of patients with ulcerative colitis (see "*Antibacterial Effect*" below).

The following effects have been found *in vitro*: inhibition of bacterial growth; inhibition of prostaglandin synthesis; increased intestinal cytoprotection due to inhibition of prostaglandin degradation; reduction of leukotriene formation; modulation of polymorphonuclear leucocyte function; inhibition of proteolytic enzymes; inhibition of DNA synthesis; and impairment of folate absorption and metabolism.

Most of these effects have also been shown in experimental animal systems. This has led to the following alternative explanations of the clinical effects of sulfasalazine.

### *Antibacterial Effect*

West *et al.*, (1974) found that the number of anaerobic bacteria in the colon lumen was markedly reduced by administration of sulfasalazine. Krook *et al.*, (1981) showed that 1 month of sulfasalazine treatment gave a drastic reduction in the anaerobic bacteria count. After four months of continuing treatment the counts returned to normal, although a decrease in certain bacterial strains was still evident.

Rheumatoid arthritis may be an enteropathogenic arthritis. One well known observation is that experimental arthritis in pigs may be caused by *Clostridium perfringens* in the large bowel. Neumann *et al.*, (1984) has recently examined the faecal flora in a normal control population and in rheumatoid arthritis patients during sulfasalazine treatment. During therapy there was a trend towards a decrease in the *Cl. perfringens* count in the sulfasalazine treated group which was not seen in the control group. Tremaine *et al.*, (1984) have recently shown that patients on sulfasalazine have a significantly lower incidence of *Cl. difficile* infection than patients with no treatment, and that a significantly higher incidence of infection is observed after antibiotic therapy.

### *Anti-inflammatory and Immunoregulatory Effect*

In recent years a large number of papers, predominantly on *in vitro* studies, have reported effects of sulfasalazine on the arachidonic acid metabolites, prostaglandins and leukotrienes.

Any equivalence to these effects *in vivo*, seen as an anti-inflammatory effect, has yet only partly been documented. Thus, inhibition of carrageenan inflammation could be demonstrated in the rat paw and in the rat colon. In the adjuvant arthritis model in rats, Steinwall *et al.*, showed a significant inhibition at high doses of sulfasalazine. Indomethacin-induced ulceration could be reduced by sulfasalazine, and water transport was normalised by sulfasalazine both in human biopsy tissue and in the dinitrochlorobenzene (DNCB) colitis in a rat model.

With regard to possible immunoregulatory effects, Holm and Perimann (1968) published a study on the effect of sulfasalazine upon lymphocytic activity. Sulfasalazine was shown to have a specific toxicity for lymphocytes, higher than for other cells. Campbell (1973) studied the effect of sulfasalazine in immunological models, and a clear immunoregulatory effect was noted.

Laursen (1978) found that sulfasalazine in mice suppressed many immunological factors, such as serum levels of different immunoglobulins and the number of lymphocytes. Rubenstein *et al.*, (1978) and Ali *et al.*, (1982) have shown that sulfasalazine therapy depresses the activity of certain lymphocytes.

## Pharmacokinetics

### *Absorption*

After the administration of a single 2 g dose of SALAZOPYRIN (enteric or non enteric coated tablets), sulfasalazine can be detected in serum within 6 hours. Two days after administration the serum concentration is negligible. With repeated daily doses, the steady state serum level of sulfasalazine is achieved after 4 to 5 days.

Sulfasalazine is poorly absorbed from the small intestine (up to 30%), after which it is excreted into the bile. A few percent of the given dose is excreted unmetabolised into the urine. The unabsorbed drug is excreted in the faeces. This is also confirmed by the observation that around 70% of an ingested dose of sulfasalazine can be recovered in the effluent of ileostomised patients. Sulfasalazine rapidly enters the enterohepatic circulation and is returned to the gastrointestinal tract via the biliary route. Up to 80% of the absorbed intact sulfasalazine can be recovered in the bile effluent.

### *Metabolism*

The 70 to 80% of the ingested dose of intact sulfasalazine which reaches the colon is subjected to azo-reductive cleavage by the colonic flora to yield the two major metabolites, 5-amino-salicylic acid (5-ASA) and sulfapyridine. Sulfapyridine is rapidly absorbed, partly metabolised in the liver, primarily by acetylation, and subsequently excreted in the urine. Non-acetylated sulfapyridine is partly protein bound. The role of the gut bacteria in splitting sulfasalazine has been elucidated in detail by Peppercorn and Goldman (1972). Thus, the delay in appearance of sulfapyridine and 5-ASA in the serum after oral administration of sulfasalazine is consistent with the time taken for the drug to reach the microbially rich colon. The two products of cleavage, 5-ASA and sulfapyridine are subsequently metabolised.

In humans only N-acetyl-5-aminosalicylic acid has been identified as a metabolite of 5-ASA. Sulfapyridine metabolites have been identified in humans as: N-acetylsulfapyridine; sulfapyridine-o-glucuronide; acetylsulfapyridine-o-glucuronide; 5-hydroxy-sulfapyridine-o-glucuronide; and N-acetyl-5-hydroxy-sulfapyridine-o-glucuronide.

The rate at which sulfapyridine is acetylated in the liver is genetically determined. Patients can be readily classified as slow or fast acetylators on the basis of the ratio of sulfapyridine and acetylsulfapyridine concentrations in serum or urine. There is also a genetic basis for differentiation of patients according to the rate at which sulfapyridine is hydroxylated. Those subjects who show relative slowness in acetylation and hydroxylation rates may be expected to show higher than normal serum concentration of sulfapyridine after administration of sulfasalazine.

### ***Distribution and Excretion***

Intact sulfasalazine can be detected in serum within 6 hours after oral administration and between 2 and 10% of a single dose can be recovered as the unchanged molecule from the urine. No detectable sulfasalazine has been found in stools of normal subjects, although up to 7% of an orally administered sulfasalazine dose has been found in the faeces of patients having ulcerative colitis. Sulfasalazine and its metabolites excreted in the urine may impart an orange-yellow colour to alkaline urine.

Most of the 5-aminosalicylate moiety formed by bacterial action in the gut is excreted unchanged in the faeces. However, up to 33% of the salicylate absorbed can be recovered in the urine almost entirely as N-acetyl-5-aminosalicylic acid.

Both sulfasalazine and 5-ASA exhibit an affinity for collagen rich tissues. It has been shown that these two entities tend to concentrate primarily in the intestinal wall as well as in the peritoneal, pleural and synovial fluids. There is also evidence that blood borne sulfasalazine can enter the intestinal lumen directly from the serum, for it has been shown by Hannagren *et al.*, (1973) that intravenously administered sulfasalazine concentrates intestinally in rats with ligated bile ducts.

The sulfapyridine formed by cleavage of sulfasalazine during azo-reduction by the intestinal flora is absorbed in the intestinal tract and appears to be evenly distributed in the various body tissues and fluids. About two thirds of the amount of sulfapyridine present in sulfasalazine is excreted in the urine, partially as acetylated or glucuronidated metabolites. The faeces contain sulfapyridine equivalent to approximately 7% of the ingested dose. There is no detectable sulfapyridine in serum 3 days after termination of treatment.

### ***Protein Binding***

Greater than 95% of absorbed sulfasalazine is bound to serum proteins.

## **INDICATIONS**

### **Ulcerative Colitis and Crohn's Disease**

Adjunct in the treatment of ulcerative colitis with the usual supportive and dietary measures. For the management of severe, acute attacks of ulcerative colitis, rectal and systemic corticosteroid therapy appears to be clinically superior to sulfasalazine, but sulfasalazine may be more effective than corticosteroids in reducing the number of relapses in patients on maintenance therapy.

In the treatment of active Crohn's disease, especially in patients with colonic involvement.

### **Rheumatoid Arthritis**

SALAZOPYRIN EN-TABS are indicated for rheumatoid arthritis which has failed to respond to non-steroidal anti-inflammatory drugs (NSAIDs).

## CONTRAINDICATIONS

Haematological, renal or hepatic dysfunction, allergic drug fever or skin eruptions due to sulphonamide derivatives including antibacterial sulphonamides, oral hypoglycaemics and thiazides.

Patients hypersensitive to sulfasalazine, its metabolites, or any other component of the product, sulfonamides, or salicylates.

Intestinal or urinary obstruction.

Patients with porphyria should not receive sulphonamides, as these drugs have been reported to precipitate an acute attack.

Children aged 2 years and younger.

## PRECAUTIONS

### Serious Infections±

Serious infections associated with myelosuppression, including sepsis and pneumonia, have been reported. Patients who develop a new infection while undergoing treatment with sulfasalazine should be monitored closely. Administration of sulfasalazine should be discontinued if a patient develops a serious infection. Caution should be exercised when considering the use of sulfasalazine in patients with a history of recurring or chronic infections or with underlying conditions which may predispose patients to infections.

### Potential Toxicity

Deaths associated with the administration of sulfasalazine have been reported, resulting from hypersensitivity reactions, agranulocytosis, aplastic anaemia, renal and liver damage, irreversible neuromuscular and CNS changes, and fibrosing alveolitis. The presence of clinical signs such as sore throat, fever, pallor, purpura or jaundice may be indications of myelosuppression, hepatotoxicity, haemolysis or other serious blood disorders. The patient should be advised to report any untoward symptoms immediately. If serious toxic or hypersensitivity reactions occur, discontinue treatment with sulfasalazine immediately while awaiting the results of blood tests. Urticaria, other skin rashes and serum sickness-like reactions may be controlled with antihistamines and, if necessary, systemic corticosteroids.

### Monitoring for Toxicity

Sulfasalazine should be administered under constant medical supervision.

Complete blood counts (including differential white cell count) and liver function tests should be performed before starting sulfasalazine tablets and every second week during the first three months of therapy. During the second three months, the same tests should be done once monthly and thereafter once every three months, and as clinically indicated. Assessment of renal function (including urinalysis) should be performed in all patients initially and at least monthly for the first three months of treatment. Thereafter, monitoring should be performed as clinically indicated.

### **Hepatic or Renal Impairment and Blood Dyscrasias**

Sulfasalazine should not be given to patients with impaired hepatic or renal function or with blood dyscrasias.

### **Hypersensitivity**

Sulfasalazine should be given with caution in patients with severe allergy or bronchial asthma.

Severe hypersensitivity reactions may include internal organ involvement, such as hepatitis, nephritis, myocarditis, mononucleosis-like syndrome (i.e. pseudomononucleosis), haematological abnormalities (including haematophagic histiocytosis), and/or pneumonitis including eosinophilic infiltration.‡

### **Drug Rash with Eosinophilia and Systemic Symptoms (DRESS)‡**

Severe, life-threatening, systemic hypersensitivity reactions such as drug rash with eosinophilia and systemic symptoms (DRESS) have been reported in patients taking various drugs including sulfasalazine. It is important to note that early manifestations of hypersensitivity, such as fever or lymphadenopathy, may be present even though rash is not evident. If such signs or symptoms are present, the patient should be evaluated immediately. Sulfasalazine should be discontinued if an alternative etiology for the signs or symptoms cannot be established.

### **Serious Skin Reactions‡**

Serious skin reactions, some of them fatal, including exfoliative dermatitis, Stevens-Johnson syndrome, and toxic epidermal necrolysis, have been reported very rarely in association with the use of sulfasalazine. Patients appear to be at highest risk for these events early in the course of therapy, the onset of the event occurring in the majority of cases within the first month of treatment. Sulfasalazine should be discontinued at the first appearance of skin rash, mucosal lesions, or any other sign of hypersensitivity.

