Idiosyncratic side effects of sulfasalazine are rare. They generally occur in the first 3 months of treatment, and symptoms may include skin rash, hepatitis, pancreatitis, pneumonitis, agranulocytosis and aplastic anaemia. These effects are usually dose-dependent. They are rarely seen in patients on low dose sulfasalazine, similar to the levels we propose to use for this study. Importantly, these side effects are generally transient and recovery is usually seen 1-2 weeks after ceasing the medication. Study participants will be monitored for the occurrence of idiosyncratic side effects in relation to taking sulfasalazine. However, as our study population will be made up of young, generally healthy women and we propose to use low doses of sulfasalazine therapy for a few weeks at most, we believe they would be at very low risk of developing these complications in relation to this study.

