Participants will be visited every 1-3 days from recruitment until delivery (while they remain inpatients) by a member of the research team to monitor for AEs or possible side effects of sulfasalazine, and to ensure the participant's ongoing willingness to participate in the trial. Participants who are discharged home prior to the birth of their baby will be reviewed by a researcher each time they attend their hospital for an outpatient review until they are readmitted or their baby is born. A member of the research team will be on call to attend or for advice relating to concerns raised by the participants or the clinicians providing their direct care.

Biochemical markers of preeclampsia disease (such as LFTs and proteinuria) will be monitored as a part of standard clinical care. The researchers will also have access to these routine pathology results – this data forms some of the secondary outcomes of the study.

The timing of delivery and any deviations from routine clinical care will be determined by the treating clinician or obstetric unit – not by a member of the research team. In the case where a member of the research team is also acting as the treating clinician, these decisions will be made in consultation with other members of the treating obstetric unit, with the best interests of mother and baby as the paramount consideration.

The medical histories of babies born to participants (including any pathology results from tests ordered by the treating clinicians) will be reviewed postnatally to assess for neonatal outcomes and AEs. A 'closing out' visit on the postnatal ward (or phone call following maternal discharge) will be made following the delivery of each participant's baby.

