## 10.2 IDENTIFYING AEs AND SAEs

All AEs/SAEs will be recorded from the time a participant signs the consent form until their postnatal closing out visit or phone call has been completed. Worsening of preeclampsia disease indicators that follow the normal, expected clinical course of the disease will not be reported as an AE/SAE, but will be recorded in the CRF. Any AE must be recorded on the AE log page in the CRF. Antenatal admission to hospital will not be considered as an AE/SAE, as it follows the course of normal clinical management for this cohort. An escalation of hospitalisation (e.g. from general ward to intensive care) as a result of an ADR will be classified as a SAE/SADR.

Participants will be asked about the occurrence of AEs/SAEs at every research team contact episode during the study, using open-ended and non-leading questions (e.g. "Tell me about how you've been feeling"), as well as specific questions relating to any occurrence of common ADRs (e.g. gastrointestinal symptoms). Participants' medication charts will be reviewed to assess for study protocol compliance, as well as any major changes to concomitant medications. AEs/SAEs may also be identified via information from the medical history or other source documents (e.g. abnormal pathology test results not consistent with the woman's preeclampsia disease progression, such as aplastic anaemia). If there is any doubt whether or not an event or clinical observation constitutes an AE, the event will be recorded as an AE.

Known, common gastrointestinal side effects of sulfasalazine therapy (nausea, vomiting, diarrhoea) will be noted on the CRF but do not need to be recorded as AEs, unless meeting the criteria for a 'serious' or 'severe' event (see *Section 10.1*).

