#### **14.6 CONTINUATION OF DRUG FOLLOWING THE END OF THE STUDY**

Not applicable – IMP administration will be ceased with the delivery of a participant's pregnancy or upon their withdrawal from the study.

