## OVERDOSAGE

The drug has low acute per oral toxicity in the absence of hypersensitivity. There is evidence that the incidence and severity of toxicity following overdosage are directly related to the total serum sulfapyridine concentration.

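### Maternal adverse-event recording ends at a closing-out contact with no minimum interval after the last dose, so it can close inside the washout period that Appendix 1 gives

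*Protocol*

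**What the plan says.** **Recording window.** Section 10.2 records all AEs and SAEs from signed consent "until their postnatal closing out visit or phone call has been completed". Section 3 describes that contact as a closing-out "visit on the postnatal ward (or phone call following maternal discharge) will be made following the delivery" of the baby. Table 2 gives it a column but no day.

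**Last dose.** Section 14.6 states that "IMP administration will be ceased with the delivery of a participant's pregnancy", or earlier if she is withdrawn.

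**Washout.** For sulfapyridine, Appendix 1 (Distribution and Excretion) states: "There is no detectable sulfapyridine in serum 3 days after termination of treatment". For the parent drug after a single 2 g dose, Appendix 1 (Absorption) states: "Two days after administration the serum concentration is negligible". Appendix 1 (Overdosage) says that "the incidence and severity of toxicity following overdosage are directly related to the total serum sulfapyridine concentration". Its Adverse Effects section adds that slow acetylators, who have higher sulfapyridine levels, may be more prone to adverse reactions.

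**Onset of reactions.** For serious skin reactions, Appendix 1 describes "the onset of the event occurring in the majority of cases within the first month of treatment". Section 1.3 says of idiosyncratic reactions: "They generally occur in the first 3 months of treatment".

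**Role in the trial.** Adverse effects in the treated mother are the first item listed under the primary objective (section 2.1.1).

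**The concern.** The recording rule is tied to a staff contact, not to time since dosing. A closing-out visit on the ward one or two days after delivery satisfies the protocol. Recording would then stop while sulfapyridine may still be in serum. After short treatment it would also stop well before a month from first dose.

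Two things are at stake. A maternal reaction that begins after closing out is never entered, so it is absent from the primary safety outcome. Observation time also differs between women for reasons unrelated to the drug: how soon they deliver, and whether closing out is a ward visit or a later call. The safety summary is meant to support a larger randomised trial (section 1.2), and with 20 women a single event changes it visibly.

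**Working it through.** **Step 1. Does anything else catch a new maternal event after closing out?**

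- Section 10.7 follows events already recorded. It does not look for new ones.
- Section 7.1 describes routine postnatal follow-up of preeclampsia, not AE collection.
- Section 7.3 plans no long-term follow-up.
- Section 10 asks women to report symptoms while they are participating, which has ended by then.

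So the closing-out contact is the only limit that matters.

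**Step 2. Inputs.**

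- Washout *W* = 3 days (Appendix 1), taken as an upper bound.
- First month = 30 days from first dose (Appendix 1 says a month of treatment; 30 is a rounding).
- *T* = days on treatment. This is an assumed range, 0.5 to 28 days. Entry needs only a judgement that the pregnancy can safely go on for more than 12 hours (section 4.2), and section 1.3 expects no more than a few weeks of treatment.
- *s* = days from last dose to closing out. This is also assumed, because the protocol gives neither a rule nor a length of postnatal stay.

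**Step 3. Washout left unrecorded** = max(0, 3 − *s*).

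- *s* = 0, 1, 2 gives 3, 2, 1 days.
- *s* = 3 or more gives 0.

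**Step 4. Part of the first month left unrecorded** = max(0, 30 − *T* − *s*).

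| *T* (days) | *s* = 2 | *s* = 5 |
|---|---|---|
| 0.5 | 27.5 | 24.5 |
| 2 | 26 | 23 |
| 7 | 21 | 18 |
| 14 | 14 | 11 |
| 21 | 7 | 4 |
| 28 | 0 | 0 |

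For example, *T* = 7 and *s* = 2 gives 30 − 7 − 2 = 21. These are calendar days without recording. They do not measure risk missed.

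**Step 5. What one unrecorded event would do at n = 20.** The exact one-sided 95% upper limit is 13.9% for 0/20 (1 − 0.05^(1/20)) and 21.6% for 1/20.

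**Step 6. Chance that at least one woman has an event after closing out** = 1 − (1 − *p*)^20. The documents give no *p*, so these are illustrations:

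- *p* = 0.1%: 2.0% (expected events 20 × 0.001 = 0.02)
- *p* = 1%: 18.2% (expected 0.2)
- *p* = 5%: 64.2% (expected 1)

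The protocol states no figure on this point, so there is none to reproduce.

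**The case against.** The case against is substantial.

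- **The onset windows describe women on treatment.** Neither the first month in Appendix 1 nor the 3 months in section 1.3 says what happens after a woman stops. A reader might take the days in step 4 as risk time missed, but the documents do not support that. Time on treatment is closely watched, with visits every 1 to 3 days for inpatients (section 3).
- **Early closing out is permitted but not shown to be usual.** Section 3 equally allows a phone call after discharge. Table 2 lists closing out after a delivery-day review that may slip to the next weekday, so after a Friday delivery that review alone may fall on day 3. A reader might infer that recording always ends within the washout. That follows only if closing out on day 1 or 2 is assumed.
- **The sulfapyridine link is limited.** Three days is an upper bound. The Overdosage statement concerns overdose, and section 1.3 places dose-related symptoms mostly above 4 g per day. Nothing ties the level to idiosyncratic rash, hepatitis or agranulocytosis.
- **The events are uncommon.** Appendix 1 calls serious skin reactions very rare, and section 1.3 calls idiosyncratic reactions rare.

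All of this stands as a limit on size. It does not supply the missing interval: no section sets one, and no section captures a later event.

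**Conclusion.** The protocol leaves the end of maternal AE/SAE recording to the timing of a staff contact. As written, recording can close with up to 3 days of the sulfapyridine washout unrecorded. When treatment is short it can also close well before a month from first dose: 21 days short for 7 days of treatment and closing out at day 2. Those figures rest on assumed values of *T* and *s*. What rests on the text alone is that no minimum interval exists and that observation time therefore varies between women.

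How many events would be lost cannot be calculated and is probably small. It would be wrong to conclude that late reactions are certainly missed, or that the documents call for a 28- to 30-day interval after the last dose; they contain no such figure.

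This cannot be left to a statistical analysis plan, because no analysis can recover events that were never recorded. The change is worth making because it is cheap and protects the first item of the primary objective.

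**What to change.** In sections 3 and 10.2 and Table 2, keep any ward visit, but let maternal AE/SAE recording end at the phone call already planned, at one fixed time for every woman. The call should satisfy both conditions:

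- *s* greater than 3 days, to clear the washout;
- *T* + *s* of about 30 days or more, to reach a month from first dose.

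A single day such as 30 days after the last dose meets both for any *T*. It is a convenient choice and does not come from the documents. Keep recording open until the call. Report maternal AEs as on drug or after last dose, with days of observation per woman.

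Cost: amended wording and one timed call for each of 20 women, using a contact that already exists. The end-of-study date moves later, since section 14.5 ties it to the last direct contact. A few women may not be reached, and section 5.6 already has a rule for loss to follow-up that can apply to them. No treatment or clinical care changes.
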